## TRIAL POPULATION

### Recruitment

A Consolidated Standards of Reporting Trials flow diagram (6) will be completed to describe patients randomized and availability of data within each arm.

### Consent

The parent or legal guardian will be asked to provide consent as soon as appropriate after randomization. This model of consent, research without prior consent or “deferred consent” is increasingly used emergency care trials in many jurisdictions (7). Once given, consent can be withdrawn at any time.

If access to medical records is declined, data collection and any linkage to national datasets will not occur. Unless removal is explicitly requested, data collected up to refusal or withdrawal will be retained, and a minimal dataset including primary outcome data will be collected. If trial continuation is refused but access to medical records is granted, data collection and linkage will continue, and the patient may be included in the analysis as appropriate.

### Baseline Patient Characteristics

Baseline data are collected at randomization directly via the Case Report Form and at PICU admission via data linkage to the U.K. Paediatric Intensive Care Audit Network (PICANet). Baseline data will be summarized by group but not subjected to statistical testing.

## ANALYSIS

### Outcome Definitions

#### Primary Clinical Outcome

The primary outcome is a composite of death and duration of IMV at 30 days postrandomization. Patients who die on or before day 30 are assigned the worst score of 31. Surviving patients are scored by the total calendar days on IMV from day 1 (randomization) to day 30, including any IMV during readmissions to PICU.

#### Secondary Outcomes

Secondary outcome measures will include mortality at various time points, duration of survival from randomization to 12 months, time to liberation of IMV, change in functional status between PICU admission and PICU discharge, days of renal replacement therapy (RRT) to 30 days, length of PICU and hospital stay and health-related quality of life (HrQoL) at 12 months (**Table 3** for details).

**TABLE 3. T3:** Secondary Outcomes

Mortality at PICU discharge	Death due to any cause before discharge from the PICU.
30-d/90-d/12-mo mortality	Death due to any cause before the relevant time point. ± 5 and ± 15 d of allowance will be considered if mortality at the exact time point is unknown, for the 90-d and 12-mo time point, respectively.
Duration of survival to 12 mo	Number of days where a patient is alive between randomization and 12 mo.
Time to liberation from invasive ventilation	Time from randomization to the start of the first continuous 48-hr period without IMV; deaths on IMV will be censored.
Functional status change between PICU admission and PICU discharge	Difference between pediatric Cerebral Performance Category and pediatric Overall Performance Category scores at admission and first PICU discharge for surviving patients.
Receipt of RRT at 30 d	Number of calendar days where RRT is received in PICU to day 30, among survivors to day 30.
Length of PICU stay	Hours until discharge plus any PICU readmissions by day 30.
Length of hospital stay	Days until discharge from any acute hospital.
Health-related quality of life at 12 mo	Assessed using child self- or parent-proxy completed age-appropriate Pediatric Quality of Life Inventory 4.0 (8), and the Child Health Utility 9D Index (9).

IMV = invasive mechanical ventilation, RRT = renal replacement therapy.

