### Sample Size

The sample size calculation used observational data from the Permissive vs. Restrictive Temperature Thresholds in Critically Ill Children with Fever and Infection (FEVER) study (4) which included 22 of 28 PICU wider National Health Service (NHS) units (*n* = 4126) and 6 months of eligible admissions.

Power estimates used 10,000 simulated trial datasets with distributions of mortality (13%) and duration of invasive mechanical ventilation (IMV) (log-normal distribution with mean = 7.8, sd = 9.5 d). To achieve 90% power, 1900 participants are required to detect a clinically meaningful mortality reduction of 2% (13–11%), and an 18-hour reduction in mean ventilator duration (7.8–7.1 d) in survivors, allowing for 10% withdrawal/refusal of deferred consent.

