### Clinical Effectiveness Analysis Methods

#### Primary Outcome

The primary clinical outcome will be summarized by arm (median, IQR, graphically) and analyzed using a two-sample rank-sum (Wilcoxon-Mann-Whitney) test (10). The primary effect estimate will be the probabilistic index, the probability that intervention is superior to control for the composite outcome, and 95% CI. The separate components will also be presented by arm with effect sizes and 95% CIs, following established guidelines (11). Mortality will be analyzed using logistic regression, adjusting for age (younger than1 yr; 1 yr to younger than 3 yr; 3 yr or older), and site as a random effect. Duration of IMV will be analyzed using a two-sample rank-sum test.

Ordered logistic regression will estimate the proportional odds ratio, adjusting for baseline variables. The unadjusted OR will be presented for comparison. If data completeness allows, the following variables will be used in adjusted analyses: predicted log odds of mortality at randomization (Paediatric Index of Mortality, version 3 [PIM-3] score (12) [continuous; linear]); primary reason for admission (suspected/proven infection vs. other); comorbidities (neurologic vs. non-neurologic vs. none); age (continuous; restricted cubic splines with four knots at the 5th, 35th, 65th, and 95th percentiles); and site (random effect).

Baseline covariates were prespecified based on anticipated associations with the outcomes. Results will be reported as adjusted odds ratios with 95% CI.

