#### Secondary Outcomes

Mortality outcomes will be compared using Fisher exact test. If suitable, logistic regression will be used, adjusted for baseline variables.

Duration of survival will be plotted as Kaplan-Meier survival curves by arm. An adjusted hazard ratio will be calculated using Cox proportional hazards regression.

Time to liberation from IMV will be reported as median time (with 95% CI) by arm using Kaplan-Meier methods. An adjusted hazard ratio will be calculated using Cox proportional hazards regression.

Change in functional status will be analyzed using adjusted linear regression, additionally adjusting for baseline status. Receipt of RRT at 30 days will be reported as median and IQR for patients surviving to day 30 and compared between groups using a Wilcoxon rank-sum test. Length of PICU and acute hospital stay will be compared using a Wilcoxon rank-sum test and reported by group using medians and IQRs in patients stratified by survival status. HrQoL score for survivors (12 mo) will be reported and a linear regression model adjusting for baseline variables will be applied to report incremental effect.

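### Time to liberation from ventilation censors deaths on IMV, so the Kaplan-Meier median overstates how quickly children come off the ventilator, and the Cox hazard ratio is not labelled cause-specific

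*SAP article*

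**What the plan says.** In the SAP article, Table 3 (Outcome Definitions, Secondary Outcomes) defines time to liberation as "Time from randomization to the start of the first continuous 48-hr period without IMV; deaths on IMV will be censored".

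Clinical Effectiveness Analysis Methods, Secondary Outcomes, gives the analysis: "Time to liberation from IMV will be reported as median time (with 95% CI) by arm using Kaplan-Meier methods", followed by "An adjusted hazard ratio will be calculated using Cox proportional hazards regression".

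The article has no cumulative incidence function, competing-risk model or sensitivity analysis for this censoring. It does not say that the hazard ratio is cause-specific.

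Other outcomes in the same article handle death differently. The primary composite gives death by day 30 the worst score, 31. Days of RRT are restricted to day-30 survivors. Length of stay is reported separately by survival status.

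**The concern.** Censoring is harmless when the censored child could still have had the event later, at the same rate as those still under observation. A child who dies on the ventilator could not. Kaplan-Meier nevertheless treats that child as someone who would have been liberated at the rate of the children who remain. Even when death is unrelated to weaning prospects, the curve and its median then describe liberation as if nobody died. They overstate how quickly children are liberated, in both arms and whether or not the arms differ.

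The Cox model has a different limitation. With deaths censored it estimates the rate of liberation among children who are alive and ventilated. That is a legitimate quantity, but it does not translate into the probability of coming off the ventilator alive, and it hardly moves when one arm has more deaths. A reader shown an unlabelled hazard ratio beside a Kaplan-Meier median is likely to read both as statements about the chance and timing of liberation.

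**Working it through.** **Inputs.** From Sample Size: "distributions of mortality (13%) and duration of invasive mechanical ventilation (IMV) (log-normal distribution with mean = 7.8, sd = 9.5 d"; the mortality target of 13% to 11%; "an 18-hour reduction in mean ventilator duration (7.8–7.1 d) in survivors"; 1900 randomised, "allowing for 10% withdrawal/refusal of deferred consent". That leaves 1900 × 0.9 = 1710 analysed, or 855 per arm if allocation is 1:1 (assumed). Not given in the article, so assumed: all deaths occur on IMV, and the log-normal describes the time at which a child would be liberated. Day 30 is used as the horizon because the primary outcome uses it.

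**Step 1. Reproduce the plan's figure.** The composite was simulated 10,000 times (IMV capped at 30, death = 31, tie-corrected rank-sum test, 855 per arm, SD 9.5 d in both arms). With an exact 18 h reduction (mean 7.05 d), power is 90.6% in whole calendar days and 91.8% on a continuous scale. With the printed mean of 7.1 d it is 87.5% and 88.3%. If the SD is instead scaled with the mean, power is about 62%. The stated 90% therefore reproduces with a common SD and an exact 18 h. It does not involve time to liberation, so nothing below changes it.

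**Step 2. What Kaplan-Meier estimates with deaths censored.**
- σ² = ln(1 + (9.5/7.8)²) = 0.910, so σ = 0.954.
- μ = ln 7.8 − σ²/2 = 2.054 − 0.455 = 1.599.
- If death is independent of weaning, Kaplan-Meier recovers the log-normal itself. The median is exp(1.599) = 4.95 d, and the day-30 value is Φ((ln 30 − 1.599)/0.954) = Φ(1.889) = 97.1%.
- Mortality appears in neither expression.

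**Step 3. What happens to the children.** Take a constant hazard λ of death on IMV, with F and f the log-normal distribution and density. Deaths by day 30 are ∫₀³⁰ λe^(−λu)(1 − F(u))du. Setting this to 0.13 gives λ = 0.0203 per day. The cumulative incidence of liberation is I(t) = ∫₀ᵗ f(u)e^(−λu)du. It reaches 50% at 5.30 d, and I(30) = 85.4%.

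At 13% mortality the median is therefore too short by 5.30 − 4.95 = 0.35 d (about 8 h). A Kaplan-Meier curve would be too high at day 30 by 97.1 − 85.4 = 11.7 points.

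**Step 4. Other mortality levels** (simulation, 200,000 per arm; the integrals in Step 3 agree to within 0.02 d and about 0.1 point):

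| Deaths on IMV | KM median (d) | Median, dead never liberated (d) | KM day 30 | Liberated alive by day 30 |
|---|---|---|---|---|
| 11% | 4.95 | 5.24 | 97.0% | 87.1% |
| 13% | 4.94 | 5.29 | 97.0% | 85.4% |
| 16% | 4.95 | 5.42 | 97.1% | 82.6% |
| 20% | 4.94 | 5.59 | 97.1% | 78.9% |
| 26% | 4.94 | 5.91 | 97.1% | 73.4% |

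**Step 5. Hazard ratios when weaning is identical and only mortality differs.**

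| Deaths on IMV | Cox, deaths censored | Subdistribution |
|---|---|---|
| 11% vs 13% | 1.00 | 0.97 |
| 13% vs 20% | 0.99 | 0.87 |
| 13% vs 26% | 1.01 | 0.78 |

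**Step 6. Sensitivity to the assumptions.** If only half of the 13% die on IMV (6.5%), Step 3 gives a median of 5.11 d and 91.3% liberated by day 30, so the gaps fall to 0.16 d and 5.8 points. If death is concentrated in children with long ventilation, the medians at 13% are 4.88 d (Kaplan-Meier) and 5.16 d, and the day-30 figures are 97.3% and 85.8%. In that scenario, 13% vs 26% deaths give a Cox ratio of 0.95 and a subdistribution ratio of 0.77.

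**The case against.** The strongest defence is that this is one secondary outcome in a plan that already accounts for death elsewhere. Several parts of that defence stand.

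- **Excess deaths are not hidden from the trial.** A reader might infer that the plan could miss a mortality cost of lower blood pressure. It could not. The primary composite ranks death worst. Mortality is analysed as a component, at four time points and as survival to 12 months. For 18% against 13% deaths (154/855 vs 111/855), the planned Fisher test gives p of about 0.005. A subdistribution hazard ratio of 0.91 with a standard error of about 0.05 on the log scale gives z = ln(0.911)/0.05 = −1.86, p of about 0.06. Mortality is the better place to look for that harm.
- **The Cox model is not wrong.** A reader might infer that its hazard ratio also describes a setting without death. It is a valid cause-specific ratio. When weaning is the same in both arms, 1.00 is the correct answer about weaning rate.
- **A day-30 percentage is not an explicitly planned output.** The plan commits to a median and a hazard ratio, so the gap in the median is the main figure. The 97% against 85% applies to any curve drawn from the same analysis.
- **At the design-sized mortality difference the between-arm effect is small.** A ratio of 1.00 against 0.97 is a difference of ln(0.97) = −0.03, less than one standard error.

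A further tempting reading concerns the separate component analysis, "Duration of IMV will be analyzed using a two-sample rank-sum test". It names no population, so a reader might infer that an early death counts as a short, favourable duration. The article does not establish this. Primary Clinical Outcome scores IMV days for surviving patients only, and Sample Size states the ventilation effect in survivors.

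None of this answers the narrower point. The planned median is still not the median time to being liberated, and the hazard ratio is still unlabelled.

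**Conclusion.** The point holds as a should-fix for one secondary outcome. Under the stated censoring rule, the Kaplan-Meier median overstates the speed of liberation in both arms: about 4.95 d against about 5.3 d at 13% mortality. Any accompanying curve would show about 97% liberated by day 30 against about 85%. These sizes rest on all deaths occurring on IMV and on the planning log-normal as the liberation distribution. The article does not give the share of deaths on IMV, and a lower share shrinks the gaps. The Cox hazard ratio is sound as a cause-specific measure, but it needs that label and a companion that reflects the chance of being liberated alive. Sample size, power and the primary analysis are unaffected.

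**What to change.** In Table 3 and in Clinical Effectiveness Analysis Methods, Secondary Outcomes:

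1. Define death before sustained 48-hour liberation as a competing event instead of a censoring event.
2. Replace the Kaplan-Meier median with Aalen-Johansen cumulative incidence of liberation by arm. Take the median as the time at which that incidence reaches 50%, so that the dead count as never liberated.
3. Report a subdistribution hazard ratio (Fine-Gray) with the same covariates as the planned Cox model.
4. Keep the Cox hazard ratio beside it, labelled as cause-specific for liberation among children alive and ventilated.

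Optionally, add a phrase to the component analysis under Primary Outcome to say that duration of IMV is compared in day-30 survivors, as Sample Size and Primary Clinical Outcome already imply.

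The cost is SAP wording and a few lines of code, with no new data. The one real downside is that a subdistribution hazard ratio is slightly harder to explain to clinical readers. The cumulative incidence curves help with that.

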## STATISTICAL PRINCIPLES

### CIs and *p* Values

The primary clinical endpoint will be tested for superiority. Secondary outcomes will be tested where specified or summarized descriptively. All tests will be two-sided with significance at *p* value of less than 0.05, and effect estimates presented with 95% CIs. No adjustments will be made for multiple testing.

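### RRT days and functional status change are compared only in survivors, so randomization does not protect either comparison, and the planned RRT median and IQR will probably say little

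*SAP article*

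**What the plan says.** In the SAP article, Outcome Definitions, Table 3 gives the RRT outcome as "Number of calendar days where RRT is received in PICU to day 30, among survivors to day 30". Under Clinical Effectiveness Analysis Methods, Secondary Outcomes, the summary follows the same restriction: "Receipt of RRT at 30 days will be reported as median and IQR for patients surviving to day 30", with a Wilcoxon rank-sum comparison. The row is titled as receipt of RRT, but no proportion receiving it is planned.

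Functional status change is the difference in category "scores at admission and first PICU discharge for surviving patients". The model is fixed: "Change in functional status will be analyzed using adjusted linear regression, additionally adjusting for baseline status". Handling of Missing Data adds a repeat with imputation, but only for patients known to be alive, so deaths stay out of both versions.

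Length of PICU and hospital stay is compared by rank-sum test and "reported by group using medians and IQRs in patients stratified by survival status". Table 3 does not restrict it to survivors, and the text does not make clear whether the test is run in all patients or within the survival strata.

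Two other sections bear on this. Sample Size builds the design on 30-day mortality falling from 13% to 11%. Primary Clinical Outcome keeps deaths in the analysis by giving them the worst score, 31.

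**The concern.** Survival is determined after randomization, and the trial's own hypothesis is that treatment alters it. If one arm saves more children, its survivor group contains children with no counterpart among the other arm's survivors, and they are likely to be sicker than average. A difference in RRT days or functional status between the survivor groups can then reflect who survived and not what treatment did to the kidney or to function. The distortion can also run the other way: if lower pressure led to deaths among children on RRT, the survivor-only comparison would flatter the harmed arm.

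The article weighs less treatment for hypotension against the risks of lower blood pressure, so these outcomes will be read partly for safety. The primary outcome avoids the problem by ranking deaths worst; these two outcomes have no death-inclusive version.

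The RRT summary is a separate matter. If most survivors never receive RRT, the median says nothing about how many did, and this is so with or without a survival effect.

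**Working it through.** **The plan's own figure.** Inputs from CIs and p Values: "All tests will be two-sided with significance at" 0.05. From Sample Size: "To achieve 90% power", 1,900 patients, mortality 13% vs 11%, log-normal ventilation time with mean 7.8 and SD 9.5 days, an 18-hour reduction, and 10% withdrawal. Equal allocation is assumed. The analysed number is 1,900 × 0.90 = 1,710, or 855 per arm. In 3,000 simulated trials (death = 31, ventilation capped at 30 days, SD 9.5 in both arms, intervention mean 7.05 days), power was 0.906 on a continuous scale and 0.908 in whole days. With the rounded mean of 7.1 days it was 0.882 and 0.874. The stated 90% is reproduced with the full 18-hour effect, so the design's survivor shares can be used below.

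**Survivors at the design effect.** 855 × 0.87 ≈ 744 and 855 × 0.89 ≈ 761. About 1,710 − 1,505 = 205 patients are left out. If the permissive target only prevents deaths and causes none, the extra survivors make up f = 0.02/0.89 = 2.25% of permissive-arm survivors.

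**Shift in RRT use from selection alone.** Let q be RRT use among other survivors and x its use among the extra survivors, with no treatment effect on RRT. Permissive-arm use is (0.87q + 0.02x)/0.89. No RRT rate is given in the documents, so q and x are assumptions.

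- With q = 8% and x = 30%: (0.87 × 0.08 + 0.02 × 0.30)/0.89 = 8.49%, a shift of 0.49 points.
- The standard error is √[0.08 × 0.92 × (1/744 + 1/761)] ≈ 1.4 points, so the shift is about 0.35 standard errors. False rejection is about 6.4% in place of 5%.

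Over a wider range, with 1,500 simulated trials per cell and 1 to 14 RRT days equally likely in recipients, the shift in points and the rank-sum rejection rate were:

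| Background use q | x = 30% | x = 50% | x = 80% |
|---|---|---|---|
| 5% | +0.56; 6.7% | +1.01; 15.1% | +1.69; 29.5% |
| 10% | +0.45; 4.8% | +0.90; 8.4% | +1.57; 17.1% |
| 20% | +0.22; 5.9% | +0.67; 5.9% | +1.35; 8.1% |
| 30% | 0.00; 5.7% | +0.45; 4.7% | +1.12; 8.1% |
| 40% | −0.22; 5.6% | +0.22; 4.6% | +0.90; 5.9% |

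**Functional status.** Day-30 survivor counts stand in for survivors to PICU discharge. If the extra survivors are d standard deviations worse, the arm mean shifts by 0.0225 × d: 0.011 SD at d = 0.5 and 0.045 SD at d = 2. The standard error is √(1/744 + 1/761) = 0.052 SD. Rejection with no true effect is at most about 14%.

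**Median and IQR of RRT days.** The median is 0 in an arm when fewer than half of its survivors receive RRT. The binomial probability that this holds in both arms is 1.00 up to 40% use, 0.99 at 45%, 0.74 at 48% and 0.24 at 50%. The probability that the upper quartile is also 0 in both arms is 0.999 at 20% use and 0.23 at 25%.

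**The case against.** The case for leaving the plan alone has weight. Deaths are not hidden: the primary outcome ranks them worst, and mortality is reported at PICU discharge, 30 days, 90 days and 12 months, so survivor results will be read beside it. The selection effect at the design difference is small, and the higher rejection rates need low background RRT use together with very high use among the extra survivors. Using a linear model for change in a category score is a choice of method. The text calls the outcome days of RRT, so the row label alone would mislead nobody.

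All of this stands as a limit on size. It does not give the RRT or functional status comparison the protection of randomization, and separate mortality figures do not show how many children who died had received RRT.

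A reader might infer three stronger things that the documents do not support.

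- That selection adds 0.02 × 0.30/0.89 ≈ 0.7 points and so manufactures harm. That sum counts the added recipients but not the baseline use that the extra survivors displace in the average; the net shift on the same inputs is 0.49 points.
- That the plan cannot detect a difference in RRT. Only the median and IQR are blind; the rank-sum test responds to the share above zero.
- That length of stay is also confined to survivors. It is not: both strata are reported, and the fault is that the tested population is unclear.

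**Conclusion.** The point holds for RRT days and functional status change. Both are compared only in patients selected by an outcome that the trial expects treatment to change, and no death-inclusive version is given. The resulting bias is modest at a 2-point mortality difference: about 0.5 points of RRT use under the 8% and 30% assumption. It matters mainly where background RRT use is low and the extra survivors often need RRT. These figures assume a survival effect in one direction, no treatment effect on RRT, and RRT rates that the documents do not give.

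The RRT median will be 0 in both arms for any use below about 45% of survivors, and the IQR 0-0 at or below about 20%. The planned summary is therefore likely to be uninformative even with no survival effect.

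For length of stay, the defect is an unstated test population. In an all-patient test an early death counts as a short stay; within strata the test conditions on survival. These are secondary outcomes and the primary is unaffected, so the change is worth making but does not threaten the trial's main conclusion.

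**What to change.** Amend Table 3 and the Secondary Outcomes analysis section as follows.

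- **RRT:** make the comparison n (%) ever receiving RRT to day 30 among all analysed randomized patients, using a logistic model adjusted for age and site as for the mortality component. Because an early death also prevents RRT, add days alive and RRT-free to day 30 with death ranked worst.
- **Functional status:** beside the survivor-only model, add an analysis with death as the worst category.
- **Length of stay:** state whether the rank-sum test is run in all patients or within survival strata. If in all patients, say that the result will not be interpreted without regard to early deaths counting as short stays.
- **Labelling:** mark survivor-only results as descriptive.

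The cost is a change of SAP wording and a little extra analysis. The outcomes involved are ones the plan already defines, and the survivor-only figures remain available to readers.
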